#### b. Patient safety culture

As stated in the introduction, a culture questionnaire may have an effect on patient safety culture. Therefore, we deploy the SCOPE questionnaire as an intervention. However, as the SCOPE questionnaire will also provide information about the prevailing culture simultaneously, we do not refrain from interpreting and using this data for analyses. Practices in the intervention arms will complete the questionnaire at the beginning of the study as a (part of the) intervention and at follow-up as a measurement tool. The practices in the control arm will only complete the SCOPE questionnaire at follow-up as measurement tool. As such, data on the development of culture will be available for the intervention groups and differences between groups will be available at follow-up.

#### c. Process evaluation

Besides the effect of the intervention we want to examine the implementation process. As a complex intervention is dependent on contextual factors we want to study these in depth to be able to address facilitators and barriers of the intervention. Therefore, we conduct interviews with the physicians and other staff of the practice.

Interviews are conducted by a semi-structured format using a topic list. Topics will examine the patient safety behaviour and culture. First the actual activities are assessed in reference to the research arm where the practice is allocated. Subsequently, patient safety themes that come up during the interview are scrutinized. For example, practices in intervention II will be questioned on their follow-up of the action plan that has been drawn during the workshop. Which activities are implemented and to which level? How did they approach this activity, and what were barriers and facilitators? Practices in the control arm will be questioned on how they perceive patient safety and on what they actually do in their practice around this theme. Interviews are held in an iterative design, by two interviewers. Every week the interviewers will discuss their data briefly to evaluate and, if necessary, to adjust the topic list accordingly [28].

### Statistical power

The power calculation for the effect of the interventions on patient safety behaviour is based on the primary outcome, incident reporting, and resulted in a power of 0.90. The following assumptions are used: 30 practices divided in three equal groups; an improvement of reported incidents in a year (from 50 [13] to 70 (intervention I) to 100 (intervention II) incidents per practice, standard deviation of 30 and an alpha of 0.05.

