**Methods/design:**

The SCOPE Intervention Study is a cluster randomized, three-armed controlled trial, that will be conducted in 30 general practices in the Netherlands. Ten practices in the first intervention arm will complete the SCOPE questionnaire and are expected to draw and implement their own improvement initiatives based on a computerised feedback report. In the second intervention arm, staff of the ten practices also will be asked to complete the SCOPE questionnaire and in addition will be given a complementary workshop. This workshop is theoretical and interactive, educating staff and facilitating discussion, leading to a practice specific action plan for patient safety improvement. The results of the SCOPE questionnaire are incorporated in the workshop. The ten practices in the control arm continue care as usual. Baseline and follow-up measurements will be conducted with an implementation period of one year. The primary outcome will include the number of incidents reported and secondary several quality and safety indicators and the patient safety culture. Moreover, interviews will be conducted at follow-up to evaluate the implementation process of the intervention.

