### Objectives

The first objective of this study is to examine the effect of two interventions on patient safety behaviour and patient safety culture in general practice: the SCOPE questionnaire solely, and the SCOPE questionnaire combined with a safety culture workshop. We conduct a three armed trial instead of a two-armed trial. The purpose of the ‘questionnaire only’ arm is twofold. Firstly, to assess whether administering a culture questionnaire with only a feedback report has an effect on patient safety behaviour and culture, compared to the control arm. Secondly, to be able to adjust for the possible intervention effect of the questionnaire in the workshop arm.

Our second objective is to evaluate the implementation process of both interventions. Designing, implementing and evaluating a patient safety culture intervention is complex. The direction of results will largely depend on the context [19-22]. Therefore, evenly important as the possible effect of the interventions is the process evaluation.

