## Discussion

The purpose of this paper is to outline the rationale and design of the SCOPE Intervention Study. This study will provide insight in the effect of conducting a safety culture questionnaire with a feedback report, on patient safety behaviour and culture in general practice. In addition, this study will reveal whether a complementary workshop to a patient safety culture questionnaire adds to the effect on safety behaviour in general practice. Lastly, interviews will shed a light on the implementation process of the interventions.

This study has several strengths. The SCOPE Intervention Study is one of the first studies that examines the effect of an intervention in primary care on patient safety behaviour and culture. Moreover, the design, a controlled trial, will provide more trustworthy results than previous studies which were observational. Another strength is that the second part of the design is qualitative and will shed light on the implementation process of the interventions. By conducting interviews with practice staff we will gain a deeper understanding on how the interventions work.

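### The single stated power of 0.90 names no test or contrast, and on the protocol's own inputs it does not hold, unadjusted, for questionnaire versus control (0.30) or workshop versus questionnaire (0.58)

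*Protocol article*

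**What the plan says.** The Statistical power section of the protocol article gives one figure for the effect of the interventions on safety behaviour: the calculation "is based on the primary outcome, incident reporting, and resulted in a power of 0.90". Its inputs are:

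- "30 practices divided in three equal groups";
- yearly reported incidents rising "from 50 [13] to 70 (intervention I) to 100 (intervention II) incidents per practice";
- "standard deviation of 30 and an alpha of 0.05".

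The section names no test, no contrast and no sidedness, and it uses no baseline correlation.

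The questions the trial is meant to answer appear elsewhere. Under Objectives, the first reason for the questionnaire-only arm is to assess "whether administering a culture questionnaire with only a feedback report has an effect on patient safety behaviour and culture", with the control arm as comparator. The second reason is "Secondly, to be able to adjust for the possible intervention effect of the questionnaire in the workshop arm". The Discussion turns this into a direct claim: "this study will reveal whether a complementary workshop to a patient safety culture questionnaire adds to the effect on safety behaviour in general practice".

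The Data analysis section plans a Poisson regression, corrected for dispersion if needed, with baseline incident count, practice size and accreditation as covariates. It mentions neither a global three-group test nor a primary contrast.

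**The concern.** A reader will take one power figure for the effect of the interventions to cover the comparisons the trial was set up to make. Three arms give three pairwise comparisons with assumed differences of 20, 30 and 50 incidents. At 10 practices per arm and SD 30, one power cannot describe all three. The smallest difference belongs to questionnaire versus control and the next smallest to workshop versus questionnaire. These are the two questions that justify having a questionnaire-only arm.

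What is at stake is how a non-significant result is read. If 0.90 is believed to apply to these comparisons, such a result looks like fair evidence that the questionnaire does nothing, or that the workshop adds nothing. With much lower power it would be inconclusive. The protocol intends to turn its results into a product with a guideline for primary care, so the distinction matters.

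**Working it through.** **Inputs.** All come from the Statistical power section: means 50 (control), 70 (questionnaire) and 100 (workshop); SD 30; n = 10 practices per arm; alpha 0.05. Two-sided testing is my assumption. The practice is the unit of the count, so no further clustering correction enters.

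**Step 1: reproduce the stated 0.90.** One-way ANOVA, global F test.

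- Grand mean = (50 + 70 + 100)/3 = 73.33.
- Noncentrality λ = n·Σ(μ − 73.33)²/SD² = 10 × (23.33² + 3.33² + 26.67²)/900 = 10 × 1266.67/900 = 14.07.
- Power from the noncentral F distribution with 2 and 27 df = **0.898**.

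This matches 0.90 with every stated input unchanged.

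**Step 2: pairwise power on the same inputs, unadjusted.** Standard error of a difference = 30 × √(2/10) = 13.42. The noncentrality is the difference divided by 13.42. Power is from the noncentral t distribution, two-sided 0.05, pooled variance on 27 df (18 df if only the two arms compared are used).

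| Comparison | Difference | Noncentrality | Power, 27 df | Power, 18 df |
|---|---|---|---|---|
| Questionnaire vs control | 20 | 1.49 | **0.30** | 0.29 |
| Workshop vs questionnaire | 30 | 2.24 | **0.58** | 0.56 |
| Workshop vs control | 50 | 3.73 | **0.95** | 0.94 |

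- The difference detectable with 80% power is about 39 incidents, larger than both 20 and 30.
- The 95% confidence interval half-width for any pairwise difference is about 2.052 × 13.42 = 27.5 incidents, taking SD 30 as known.
- The probability that questionnaire vs control and workshop vs questionnaire are both significant is about 0.12 (simulation, 200,000 trials).

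**Step 3: alpha and sidedness.** One-sided 0.05 gives 0.42 for questionnaire vs control and 0.70 for workshop vs questionnaire. Two-sided 0.025 gives 0.21 and 0.46. No variant brings either near 0.90.

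**Step 4: the planned baseline adjustment.** Treat SD 30 as unadjusted and assume a correlation ρ between baseline and follow-up counts. The residual SD is then 30 × √(1 − ρ²), tested on 26 df. The document gives no ρ, so these values are assumptions.

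| Assumed ρ | Residual SD | Questionnaire vs control | Workshop vs questionnaire |
|---|---|---|---|
| 0.5 | 26.0 | 0.38 | 0.70 |
| 0.7 | 21.4 | 0.52 | 0.85 |
| 0.9 | 13.1 | 0.91 | >0.99 |

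**Step 5: sensitivity to the number analysed.** With 9 or 8 practices per arm, λ falls to 12.67 or 11.26 and the global power to 0.86 or 0.80.

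**The case against.** The strongest objections concern how far the figures reach, not the arithmetic.

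1. *The test is inferred.* A reader might conclude that 0.90 can only be the power of a global test. The document does not support that, because it names no test and other readings also land close: workshop vs control at two-sided alpha 0.025 gives 0.905, and both interventions pooled vs control, one-sided at 0.05, gives 0.902. The first departs from the stated alpha. Neither is questionnaire vs control or workshop vs questionnaire, so the uncertainty about the source does not rescue the figure for those two.

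2. *One comparison within the objectives is well powered.* This is right. The first objective covers the effect of both interventions and so includes workshop vs control, at about 0.95. A reader might infer that the trial is underpowered for its objectives as a whole, which goes too far. It is also fair that Objectives names questionnaire vs control outright but only implies workshop vs questionnaire. The explicit statement of the latter is in the Discussion.

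3. *The planned analysis adjusts for baseline.* This stands and is the most important qualification. It is tempting to read 0.30 and 0.58 as the power of the trial as designed, so that true effects would be missed about 7 and 4 times in 10. Those rates describe an unadjusted comparison. With a moderately high correlation, workshop vs questionnaire could be adequately powered. Questionnaire vs control would need a correlation of about 0.9.

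4. *Drop-out.* The offer of workshops after the study is a measure to prevent selective drop-out and forecasts no losses. The figures for 9 and 8 practices per arm therefore show sensitivity only and are no evidence of an error.

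5. *The analysis plan may settle the hierarchy of contrasts.* It may, and its absence from the article is not the point. The point is a stated figure attached to a broader claim than it can carry.

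**Conclusion.** The point holds in a limited form. The protocol states one power of 0.90 without saying what it is the power of. A global three-group F test reproduces it (0.898) and is the likely basis, but this needs confirming. On the same inputs, without baseline adjustment and with two-sided alpha 0.05, power is about 0.95 for workshop vs control, 0.58 for workshop vs questionnaire and 0.30 for questionnaire vs control. The 0.90 therefore does not apply to the last two.

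Baseline adjustment raises these figures by an amount the document does not allow one to compute. It may well resolve workshop vs questionnaire. It resolves questionnaire vs control only if the baseline correlation is about 0.9. The documents do not support saying that the trial is underpowered throughout, or that the unadjusted figures are its actual power under the planned model.

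**What to change.** In Statistical power:

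- State which test the 0.90 refers to. If confirmed, say that it is the global test on 2 degrees of freedom with all 30 practices analysed.
- Add the three pairwise powers: 0.95 (workshop vs control), 0.58 (workshop vs questionnaire) and 0.30 (questionnaire vs control), labelled as unadjusted. Alternatively, give adjusted values together with the baseline correlation assumed and its source.
- Optionally add 0.86 and 0.80 for the global test with 9 and 8 practices per arm, labelled as a sensitivity range.

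In the reporting plan, present questionnaire vs control as an estimate with a 95% confidence interval and state that a non-significant result is inconclusive. Treat workshop vs questionnaire the same way unless a stated baseline correlation supports adequate power.

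In the Discussion, replace the promise that the study will show whether the workshop adds to the questionnaire with wording that it will estimate that added effect, with its uncertainty.

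The cost is wording only. The stated figures become less favourable, but no extra practices and no change to conduct or data collection are needed.

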### Ethical approval

The Medical Research Ethics Committee of the University Medical Center Utrecht concluded that the Medical Research Involving Human Subjects Acts does not apply.

### Implementation of study results

The results of the SCOPE Intervention Study will result in a self-employable product with a guideline that can be used by professionals in primary care to improve their patient safety and culture. To transfer the knowledge acquired during this study among general practitioners we will organize a meeting with representatives of the primary care professional associations other than of general practice. Here, we will present our results and discus possible adjustments of the tool and possible additional information needed to shape the workshop so that these professions in primary care, such as physiotherapy and midwifery, can use this tool as well.

### Data analysis

To analyse the number of reported incidents we will use a poisson regression, if necessary, the analysis will be adjusted for over- or underdispersion [29]. Baseline characteristics such as number of incidents, size of the practice and accreditation will be included as confounders. Where possible we will adjust for baseline measurement of patient safety culture. We will describe patient safety behaviour measured by complaints, meetings and other quality and safety indicators and compare baseline with follow-up. The development of patient safety culture in the two intervention groups and differences in culture between the three arms at follow-up will be analysed by mean scores of the dimension using mixed linear models. All analyses will be corrected for clustering within practices. If necessary a multiple imputation technique will be used for missing data. Data collected from staff during the interviews will be transcribed and analysed with thematic content analysis using software NVivo to code and analyse the data [30].

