## Methods/design

### Design and setting

The SCOPE Intervention Study is a cluster randomized, three-armed controlled trial complemented with a qualitative study. The study will be conducted in thirty general practices in the Netherlands.

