### Measurements

#### a. Patient safety behaviour

The primary endpoint is the number of incident reports reported by staff in the practice. This endpoint is chosen as incident reporting gives an indication of the patient safety behaviour and culture in the practice. We hypothesize that an increase of reported incidents corresponds to an open patient safety culture. Secondary endpoints are the presence of quality and safety indicators in the previous year such as ‘the presence of a procedure for complaints’, ‘how often safety was on the agenda and/or discussed during team meetings’, ‘whether a safety management policy was present’ and ‘whether safety was subject of staff education’. These outcomes are measured using a practice questionnaire at baseline and follow-up in all study arms.

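### The only comparison stated for the secondary safety-behaviour indicators is baseline with follow-up; no contrast between the randomised arms is named

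*Protocol article*

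**What the plan says.** The section on patient safety behaviour makes the indicators endpoints of the trial: "Secondary endpoints are the presence of quality and safety indicators in the previous year". It gives as examples a complaints procedure, how often safety was discussed at team meetings, a safety management policy, and safety as a subject of staff education. It then states: "These outcomes are measured using a practice questionnaire at baseline and follow-up in all study arms".

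The Data analysis section has one sentence on analysing them: "We will describe patient safety behaviour measured by complaints, meetings and other quality and safety indicators and compare baseline with follow-up". The next sentence, on culture, lists development over time in the two intervention groups and, separately, a contrast between arms: "differences in culture between the three arms at follow-up will be analysed by mean scores of the dimension using mixed linear models".

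The first objective is to "examine the effect of two interventions on patient safety behaviour and patient safety culture in general practice". For the questionnaire-only arm, the question is whether it "has an effect on patient safety behaviour and culture, compared to the control arm".

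**The concern.** The trial is randomised with a control arm, and the data needed for a controlled comparison of these indicators are collected. Yet the one comparison named for them runs over time, not between arms. That comparison cannot answer an objective framed against control.

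At stake is how the indicator results can be interpreted. The two measurements are separated by a one-year implementation period. In that time practices may change for reasons unrelated to the interventions. The article itself supplies plausible reasons: practices may hold or pursue accreditation, volunteers are likely to be the most motivated, and the Background argues that administering a survey can itself act as an intervention. All arms complete a practice questionnaire at baseline, so even the control arm may respond to being asked. The Discussion presents the controlled design as an advance on earlier observational studies. For these indicators, a before-after comparison alone would give up that advantage.

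**Working it through.** **The plan's own figures.** No figure is given for these indicators, so there is none to reproduce. The only design figure is the power of 0.90 for incident reports. It reproduces as the overall F test of a one-way analysis of variance with means 50, 70 and 100, SD 30, 10 practices per arm and alpha 0.05. The grand mean is 73.33, and the noncentrality is 10 × (23.33² + 3.33² + 26.67²) / 30² = 14.07 on 2 and 27 degrees of freedom, giving power 0.898. The present point does not touch it.

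**The stated analyses side by side.**

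| Outcome | Comparison stated in Data analysis | Uses randomisation? |
|---|---|---|
| Incident reports (primary) | Poisson regression, baseline incidents, practice size and accreditation as covariates | Not described as before-after |
| Culture (secondary) | Development over time in the two intervention groups, and the three arms at follow-up, mixed linear models | Yes, for the three-arm comparison |
| Practice indicators (secondary) | Described; baseline with follow-up | None named |

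**What each comparison estimates.** Let *s* be the change over the year that would occur without intervention, the same in expectation in all arms because of randomisation. Let *d1* and *d2* be the effects of the questionnaire alone and of the questionnaire plus workshop.

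- Before-after change: control *s*; questionnaire arm *s + d1*; workshop arm *s + d2*.
- Before-after change pooled over three equal arms: *s + (d1 + d2)/3*.
- Difference between arms: *d1* (questionnaire vs control), *d2* (workshop vs control), *d2 − d1* (workshop vs questionnaire).

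Read as an effect, the before-after change in an intervention arm is wrong by exactly *s*. In the difference between arms *s* cancels.

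**Range for *s*.** The article gives no figure for secular change, so these values are assumptions, in percentage points of practices having an indicator.

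| *s* | True effect *d2* | Before-after, workshop arm | Workshop minus control |
|---|---|---|---|
| 0 | 0 | 0 | 0 |
| +10 | 0 | +10 | 0 |
| +20 (40% to 60%) | 0 | +20 | 0 |
| −20 | +20 | 0 | +20 |

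The last row shows that the error can also hide an effect.

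**Precision of the controlled comparison.** Assume 60% of practices in each arm have an indicator at follow-up, with 10 practices per arm. Unadjusted, by the normal approximation, the standard error of a difference is √(2 × 0.6 × 0.4 / 10) = 0.219, and the 95% half-width is 1.96 × 0.219 = 0.43, or about 43 percentage points. Baseline adjustment may narrow this, but the estimates will remain imprecise.

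**The case against.** The strongest reply is that the sentence promises only description. No test, model or confirmatory claim is attached to these indicators, unlike incidents and culture in the same section. The indicators are measured in all arms and the objective refers to control, so the authors may well intend to show each arm's change side by side, control included. The article is also a condensed account, and the model for minor secondary indicators can be left to a fuller plan. With 10 practices per arm, keeping them descriptive is defensible.

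Much of this stands, and it limits the point. A reader might infer that the plan will present before-after change as an intervention effect, or has decided against using the control arm here. The document says neither; both are risks left open by the wording. A reader might also infer that within-arm significance tests are planned, and attack those, but none is specified. A reader might add regression to the mean, but the eligibility criteria (practice size, at least one GP, no recent SCOPE questionnaire) do not select practices on low indicator values. Finally, a reader might conclude that no secondary outcome gets a controlled comparison; culture does.

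What does not stand is that this is merely detail left out. The article names a comparison, and the one it names does not match the objective. The adjacent sentence on culture shows that the authors state a contrast between arms where they want one.

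**Conclusion.** The point holds for the secondary practice-level behaviour indicators only. As worded, the planned comparison does not estimate either intervention's effect on them, although the control data to do so will be available. If before-after change were read as an effect, the error would equal the whole secular change over the year; its size is unknown from the document, and the 20-point example is an assumption. That the error cancels between arms rests on randomisation making the secular change equal across arms in expectation.

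The primary analysis, its power and the follow-up comparison of culture are unaffected. Because the indicators are secondary and described rather than tested, this is a correction that should be made, but not one on which the trial's validity depends.

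**What to change.** In Data analysis, replace the baseline-with-follow-up comparison of the indicators with wording such as: *For each quality and safety indicator the randomised arms will be compared at follow-up, adjusted for the practice's baseline value of that indicator and, where the data allow, for practice size and accreditation. A small-sample method will be used for binary indicators. Differences between arms will be reported with 95% confidence intervals and regarded as exploratory. Change from baseline will be shown by arm, including control, as description only.*

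The qualifier on the stratification factors matters, because a binary model on 30 practices supports few terms. Treating the results as exploratory avoids implying firm claims across several indicators.

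The cost is one paragraph and slightly more analysis, with no new data. The downside is that the intervals will be wide and should be presented as such.
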